## Abstract

**Background:**

Hypertension is the most frequent chronic pathology in France and in the world. It is one of the main modifiable cardiovascular risk factors. In France, 50% of treated hypertensives are uncontrolled and only 30% of treated patients are fully adherent to their antihypertensive treatment. Poor adherence to drug treatments is considered as one of the main causes of non-control of hypertension. Since 2018, a new profession has entered the French healthcare system: advanced practice nurses (APN). They have many broad-based skills, at the interface of nursing and medical exercises. The purpose of this study is to assess the impact of an APN intervention versus usual care on hypertension control.

**Methods:**

The study will take place at the Hôtel-Dieu University Hospital, Paris, France, as prospective, open-label, controlled, randomized 1-to-1, monocentric, and superiority trial. The participants will be recruited during day hospitalization for cardiovascular assessment in the context of their hypertension management. Patients will be divided into two groups: a “usual care” group which will continue traditional follow-up (day hospitalization followed by consultation with a medical doctor (MD) within approximately 2–12 months) and an “intervention” group which will meet an APN between the day hospitalization and the MD consultation. Participants will be monitored until 12 months after the day hospitalization, depending on their last follow-up study appointment (MD consultation). The primary outcome is the rate of controlled BP (BP < 140/90 mmHg in office BP measurement) in each group. The hypothesis formulated is that an individual APN intervention, included in usual hypertension management, improves hypertension control.

**Discussion:**

This innovative study will be the first in France where APNs are beginning to be established in the healthcare system. It will provide an objective look at this new profession and the impact it can have in the framework of global management of hypertension.

**Trial registration:**

ClinicalTrials.gov NCT0448249. Registered on June 24, 2020.

## Background

Hypertension is defined by blood pressure (BP) ≥ 140/90 mmHg in office BP measurement after repeated consultation and/or BP ≥ 135/85 mmHg by home BP monitoring regardless of antihypertensive drug use [1–4]. It is the most prevalent chronic pathology in France and in the world [3]. It is the main modifiable cardiovascular, cerebrovascular, renal, and neurodegenerative risk factor and accounts for 13% of mortality worldwide (more than 10 million deaths) [5, 6].

In France, in 2015, the prevalence of hypertension was 31.3% of people aged between 18 and 74, according to ESTEBAN, a cross-sectional study implemented by Santé Publique France, a national public health agency, from 2014 to 2016 on a representative sample of the French population. Among these hypertensive adults, 43.7% were unaware of hypertension, and only 50.3% of those treated were controlled. Only 33.6% of treated hypertensive patients were considered adherent [7]. This rate is similar for all the main cardiovascular risk factors, such as type 2 diabetes and dyslipidemia [8, 9].

Nearly 200 countries, including France, have joined the World Health Organization Global Plan of Action for the Control of Non-Communicable Diseases 2013–2020. Reducing the prevalence of hypertension is one of the targets of this project through the implementation of policies promoting a healthier lifestyle: weight control, increased physical activities, healthy diet, alcohol consumption reduction, and tobacco fight strategies [10].

Poor adherence to drug treatments is considered as one of the main causes of uncontrolled hypertension. Non-adherence can affect up to 80% of hypertensive patients [1] and is often defined by taking less than 80% of the days covered by prescribed medication. Early discontinuation of treatments, suboptimal daily use of the prescribed regimens, and difficulties in adapting a healthy lifestyle according to the recommendations are the main aspects of non-adherence [1, 2]. Lifestyle changes are known to prevent or delay the onset of hypertension and cardiovascular complications. Recent recommendations including the 2018 Guidelines for the Management of Arterial Hypertensions of the European Society of Hypertension promote healthy behaviors [1–3].

These deficiencies in therapeutic adherence and disease objective control can be explained by a person’s inability to take his or her treatment, including socioeconomic constraints, hostility, depression, and anxiety. Factors associated with poor adherence include low educational level and social isolation [3, 11–16]. Widely spaced consultations of short duration and lack of time for health education and for close monitoring are deleterious for long-term hypertension control and therapeutic alliance development [17].

Health education for hypertension management is considered as one of the best ways to prevent cardiovascular complications [18]. Hypertension can be asymptomatic; it is necessary to inform patients about its possible complications so as to involve them in monitoring [4]. In addition, the chronic aspect of hypertension complicates its management. It can be difficult for patients to admit their vulnerability, to take long-term daily treatment, and to conduct adequate monitoring. For a better hypertension control, it seems necessary to improve management and to reinforce the therapeutic alliance. Better communication between caregivers and patients is conducive to accurate diagnosis, treatment choice, adherence, and patient satisfaction [19]. It is possible to improve this aspect of comprehensive care through personalized, in-depth health education.

Since July 2018, a new profession has emerged in the French healthcare system: advanced practice nurses (APN). This profession has existed for several decades in other countries such as Canada, the USA, Australia, and the UK. These countries have already established this profession in their healthcare system, even institutional several protocols related to advanced nursing practice. The International Council of Nurses defined APN in 2002 as follows: “An APN is a State-certified or certified nurse who has acquired the theoretical knowledge, the know-how necessary for making complex decisions, as well as the clinical skills essential to the advanced practice of his profession, advanced practice whose characteristics are determined by the context in which the nurse will be authorized to practice” [20]. This definition identifies the bases of this exercise while leaving each country free to adapt this practice according to the context and its needs in terms of health [21].

In France, APN training and exercise are based on National Decree No. 2018-629 [22]. APNs have many broad-based skills, at the interface of nursing and medical practice. These new skills allow them not only to prescribe and interpret additional exams, but also to renew prescriptions introduced beforehand by a medical doctor (MD). APNs can monitor patients suffering from chronic pathologies, such as hypertension, alternating with MDs in the framework of a commonly established organizational protocol.

This new profession in France has appeared in a context marked by several public health challenges, such as a decreased number of MDs and increased chronic pathologies over time with the aging of the population.

This article introduces the protocol of a study aimed at assessing the impact of an APN intervention, as part of usual care, on hypertension control.

## Methods

### Conception of the study

The study was conceived by a team of doctors and an APN working at the Diagnosis and Therapeutic Center of the Hôtel-Dieu University Hospital, Assistance Publique – Hôpitaux de Paris, France. This department is one of the labeled European centers of excellence for hypertension.

A pilot study lasting several months was carried out in the department in 2022. It allowed us to develop the protocol, thanks largely to the patients involved, whose opinions were solicited. It has not been published.

The protocol has been reviewed following the SPIRIT guidelines.

### Study design

This study will be a prospective, open-label, randomized 1-to-1, controlled, and monocentric superiority trial, conducted at the Diagnosis and Therapeutic Center of the Hôtel-Dieu University Hospital, Assistance Publique – Hôpitaux de Paris, France (Fig. 1).

**Fig. 1 Fig1:**
[figure not shown]
Study process

Recruitment should start during spring 2023 and last approximately 1 year.

### Participants

The patients will be recruited during their visit to the day hospitalization section of the Diagnosis and Therapeutic Center of Hôtel-Dieu University Hospital, for hypertension-related complications and cardiovascular risk assessment as part of their hypertension management.

Participants will be eligible if they are at least 18 years of age, diagnosed with hypertension (treated or untreated), followed by a MD in the structure for hypertension management, and able to provide written informed consent. Hypertension is defined by BP ≥ 140/90 mmHg by office BP measurement and/or BP ≥ 135/85 mmHg by home BP monitoring.

The non-inclusion criteria will be patients under 18 years old, APN follow-up prior to day hospitalization, pregnancy, guardianship/curatorship, or inability to give free informed consent.

Written information and oral explanations will be given to patients. To complete their inclusion in the study, free informed and written consent will be collected from each participant during the day of hospitalization.

The dropout criteria will be an acute cardiovascular event during the study period and/or therapeutic adjustment of hypertension treatment by another health professional than the APN or MD referent during the study period and/or refusal to proceed in the study.

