The APN will then assess the lifestyle and advise the patient according to the latest recommendations [1–3, 23]:Salt consumption limitation (about 6 to 8 g a day)Weight reduction in the event of overweight or obesity to maintain a normal body mass index (between 18.5 and 24.9)Practice of regular physical activity of approximately 30 min a day (to be adapted according to the clinical condition of the patient)Alcohol consumption limitation to less than 14 units per week for men, 8 units per week for womenEstablishment of a diet rich in fiber and low in saturated fatSmoking cessation

Patients’ knowledge about drugs, their indications, and mechanisms will be evaluated and updated if necessary. To estimate the overall risk of drug interaction, the APN will ask the patient about a possible additional prescription or self-medication.

While posology adaptation in the event of side effects or uncontrolled hypertension will be carried out when necessary, the APN will refer the patient to the MD if an introduction of a new drug is needed.

The APN will propose to the patient a decision-making balance between benefits and risks, the objective being to encourage the patient to improve therapeutic adherence, to promote a healthy lifestyle, and to establish in coordination with the patient a treatment plan to improve adherence.

The end of the patient interview will be dedicated to unmentioned questions or subjects, requiring in-depth consideration.

The APN will give the patient a new home BP monitoring sheet with a reminder of the procedure to follow. The patient will be required to bring the results to his or her next MD consultation.

The APN intervention report will be digitally available in the patient’s electronic medical file.

If a participant does not show up for the APN intervention, we will call him/her to schedule another appointment in the limit of the data collection timeframe. If he/she still does not show up, the allocation group will remain the same. The rate of participants not having shown up for the APN intervention will be mentioned in the result.

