**Fig. 3 Fig3:**
[figure not shown]
Plan for the MD consultation

Before the MD consultation, a healthcare giver (usually a nurse) will perform an office BP measurement according to the protocol described in the “Outcomes” section. An ECG will likewise be performed before the MD consultation.

The MD will proceed to the physical examination and evaluate drug treatments, tolerance, efficacy, and eventual modifications since the previous appointment.

He will check the home BP monitoring and other paraclinical exams such as ECG or blood test. While home BP monitoring is usually considered superior, according to its quality and taking into account potential masked or white coat hypertension, either the office BP measurement or home BP monitoring will be preferred by the MD to evaluate the BP level and the efficacy of the antihypertensive drugs taken during the study [1, 2].

The MD will carry out a summary of the medical history since the last follow-up, an assessment of the cardiovascular risk factors, and a clinical summary.

Finally, the MD will prescribe medication and paraclinical exams, if needed, for the next appointment.

If a participant does not show up for the MD consultation, we will call him/her to schedule another appointment in the limit of the data collection timeframe. If he/she still does not show up, the participant will be considered lost to follow-up.

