### Data monitoring committee

As the procedure cannot cause any adverse effects, no early termination is planned.

Data quality control on the case report form during statistical analysis will be performed to ensure that the data are complete, consistent, and plausible. In the event of an anomaly, the investigator will be asked to correct it. If a check is required in a source document, it can only be done by a member of the supervisory medical team.

An audit may be carried out at any time by persons designated by the sponsor and independent of those responsible for the research. The persons leading and monitoring the research agree to comply with the sponsor’s audit requirements. Verification can be applied at all stages of the research, from the development of the protocol to the publication of results and the classification of data used or produced in the research.

Any event resulting from a breach of protocol, standard operating procedures or applicable laws and regulations by an investigator, or any other person involved in the conduct of the research shall be subject to a no-action promoter compliance report (Assistance Publique – Hôpitaux de Paris). These non-conformities will be managed in accordance with the sponsor’s procedures.

The final report of the research with the human person referred to in Article R1123-67 of the CPMP shall be prepared and signed by the sponsor and the investigator. A summary of the report shall be prepared in accordance with the reference plan of the competent authority and shall be sent to the latter within one year of the end of the research, corresponding to the end of the participation of the last person having lent himself to the research.

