### Statistical analysis

Data scientists will remain blinded by means of two databases:One database for all the participants with the data of the day hospitalization and the MD consultation (including the primary outcome). To maintain blinding, the groups will be called “group A” and “group B”One database with only the data of the APN intervention, so as to perform statistical analysis specific to this stage

The primary outcome measure (difference in rate of controlled BP between “intervention” and “usual care” groups) will be analyzed using a chi-square test. A *p* value < 0.05 will be considered significant. Participants with missing data for this primary outcome will be excluded.

For secondary outcome measures, the rate of performance and quality of the home BP monitoring between the “intervention” and “usual care” groups will be analyzed using a chi-square test. The difference between average BP at baseline and at follow-up will be determined for all the patients and separately for patients in the two study groups. Differences between baseline and follow-up will be tested for significance within paired *t*-tests within each group. Proportions of therapeutic adjustments and their indications between the “intervention” group and the “usual care” group will be tested for significance using a *t*-test for independent samples. For these secondary outcomes, missing data will be replaced by the mean and the standard deviation calculated on the sample, in case of quantitative variables, and neglected for the qualitative variables.

Non-adherent participants (APN intervention missed for the “intervention” group) will be considered in the statistical analysis: the rate of non-adherent participants will be mentioned in the results.

No adjustment for baseline differences is scheduled following the randomization. Nevertheless, statistical analysis may highlight participant characteristics, which we can correlate to controlled BP. If needed, an adjustment for baseline differences will be performed at a later time.

Correlations between the performance and quality of home BP monitoring in MD consultation and controlled BP will also be analyzed.

No interim analyses are scheduled.

Statistical analysis will be carried out using the R software.

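### Two post-randomisation events plausibly tied to blood pressure, one of them also to arm, are dropout criteria, so the complete-case primary test may not compare the groups as randomised

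*Protocol article*

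**What the plan says.** All references are to the protocol article.

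- **Participants:** "The dropout criteria will be an acute cardiovascular event during the study period and/or therapeutic adjustment of hypertension treatment by another health professional". Changes made by the APN or by the patient's own MD in the unit are exempt. There are three criteria in all: an acute cardiovascular event, a drug adjustment by an outside professional, and refusal.
- **Randomization:** the envelope is opened as the last step of the day hospital visit, after consent. All three events therefore fall after allocation.
- **Outcomes:** the primary outcome is controlled office BP at the MD consultation, 2 to 12 months later.
- **MD consultation:** for a patient who misses the visit and the rescheduled one, "If he/she still does not show up, the participant will be considered lost to follow-up".
- **Statistical analysis:** the primary outcome is compared by chi-square, and "Participants with missing data for this primary outcome will be excluded".
- **APN intervention:** for a patient who misses the APN visit, "If he/she still does not show up, the allocation group will remain the same". The Statistical analysis section adds that such patients "will be considered in the statistical analysis: the rate of non-adherent participants will be mentioned in the results".
- **APN intervention, on drugs:** "While posology adaptation in the event of side effects or uncontrolled hypertension will be carried out when necessary". A dose change by the APN is thus part of the tested intervention and is not a dropout event.
- **Sample size:** 150 per arm, raised to 165 per arm by a 10% margin for loss to follow-up.

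**The concern.** Randomisation protects the comparison only if the patients analysed are those randomised, or if those missing are missing for reasons unrelated to arm and outcome. The dropout rule removes patients for reasons plausibly related to both.

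**Outcome.** The Background section calls hypertension the main modifiable cardiovascular risk factor. An acute cardiovascular event, or an outside prescriber changing antihypertensive drugs, is plausibly related to how well BP is controlled.

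**Arm.** A dose change made by the APN keeps the patient in the trial, while the same change made by an outside professional is a reason to drop the patient. Only the intervention arm has a scheduled visit between the day hospital and the MD consultation. Usual-care patients may therefore turn to outside prescribers more often. On the other hand, the APN asks about additional prescriptions, so outside adjustments may be detected more often in the intervention arm. These mechanisms pull in opposite directions, and nothing in the document shows which prevails.

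If the patients removed differ between arms in number or in BP control, the chi-square test carries a selection effect. Masking the data scientists to group labels cannot undo this, because the patients are already gone.

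**Working it through.** **1. The rules side by side.** A patient who misses the APN visit is kept in the allocated group. A patient with a cardiovascular event or an outside adjustment is a dropout. If no final office BP is then recorded, the missing-data rule excludes that patient. The intention-to-treat handling therefore covers one kind of post-randomisation event and not the other two.

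**2. The plan's allowance.** 300 × 1.10 = 330, which reproduces the stated recruitment target. The margin is named as loss to follow-up. The Sample size section does not say whether dropouts under the Participants criteria are inside it.

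**3. Bias from unequal dropout (all dropout figures assumed).** Let p be true control in an arm, d the fraction dropped and c the control rate among those dropped. The rate observed among those left is

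(p − d × c) / (1 − d).

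With no true effect, p = 0.50 in both arms (the plan's usual-care rate), and c = 0.30:

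| Dropped, usual care / intervention | Observed usual care | Observed intervention | Intervention − usual care |
|---|---|---|---|
| 15% / 5% | (0.50 − 0.045)/0.85 = 0.535 | (0.50 − 0.015)/0.95 = 0.511 | −2.5 points |
| 10% / 5% | (0.50 − 0.030)/0.90 = 0.522 | 0.511 | −1.2 points |
| 5% / 3% | 0.511 | (0.50 − 0.009)/0.97 = 0.506 | −0.4 points |

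With c = 0.70 and 15% / 5%, the rates are 0.395/0.85 = 0.465 and 0.465/0.95 = 0.489, a difference of +2.5 points. The sign depends on who is dropped and from which arm. If 10% are lost at random in both arms, the bias is zero.

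**4. Effect on the test (assumed).** Suppose one arm loses 10% of its uncontrolled patients and the other loses none, with 50% true control in both and 165 randomised per arm. The affected arm shows 0.50/(0.50 + 0.50 × 0.90) = 0.526, a spurious 2.6 points. By normal approximation, the two-sided 5% chi-square test then rejects in about 7.6% of trials.

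**5. What the complete-case result leaves open (assumed).** Suppose 10% are missing in each arm and the observed rates equal the planned 50% and 65%. Over all randomised patients:

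- Missing = not controlled in both arms: 0.90 × 0.65 − 0.90 × 0.50 = 0.585 − 0.450 = 13.5 points.
- Extreme against the intervention (its missing patients uncontrolled, those in usual care controlled): 0.585 − (0.450 + 0.10) = 3.5 points.
- Extreme in its favour: (0.585 + 0.10) − 0.450 = 23.5 points.

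**The case against.** Several stronger readings are tempting, and the document does not support them.

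- **That every dropout is expressly excluded.** A reader might infer this, but the text does not say that a dropout who still attends the MD consultation is left out. The missing-data rule removes only patients without the outcome. This objection stands as a limit. Exclusion is the natural meaning of a dropout criterion, but the point rests on that reading. If attending dropouts are to be analysed, the plan should say so.
- **That usual-care patients have no contact with the unit for up to a year.** The Home BP monitoring section lets any participant contact the unit if concerned, 12 months is the upper limit, and adjustments by the referent MD are exempt in both arms. What remains is the lack of a scheduled intermediate visit. More outside adjustments in usual care is a plausible assumption, not a documented fact.
- **That these losses come on top of the 10% margin.** The document is silent on this.
- **That the bias is large.** The 15% / 5% pair averages 10%, so these rules alone would use up the whole margin (165 × 0.15 + 165 × 0.05 = 33 patients, against 30 added). Lower pairs give about a point or less.
- **That patients with the worst outcome are removed.** The endpoint is office BP control, and nothing shows that patients with a cardiovascular event have worse BP at the final visit.
- **That harm is hidden.** The Data monitoring committee section says "As the procedure cannot cause any adverse effects, no early termination is planned". Whether that is sound is a separate matter from the primary comparison. A dropout is also not an unrecorded event, since an explanation is required for any missing data.

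It can also be said that only an article is at hand, and that analysis sets are commonly left to the full protocol or the analysis plan. That is fair for what is absent. The dropout criteria and the complete-case rule, however, are stated here, and no passage repairs their combined effect.

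**Conclusion.** The concern holds in this form. The plan names two post-randomisation events as reasons for dropout. Both are plausibly related to BP, and one is plausibly related to arm. It also excludes missing primary outcomes. On the natural reading, the primary test no longer compares the groups as randomised, although the plan keeps patients who miss the APN visit in their group.

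Neither direction nor size can be derived from the document, which gives no dropout rates. Under the stated assumptions (50% true control in both arms, 30% among those dropped) the spurious difference runs from about 0.4 to 2.5 points, against a planned effect of 15. These figures illustrate and do not predict. The conclusion rests on reading dropout as leaving follow-up, and on the two events being related to BP and arm. It does not depend on whether the sample size is right.

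**What to change.** **Participants.** Restrict withdrawal from follow-up and analysis to refusal to proceed. Record acute cardiovascular events and outside adjustments of antihypertensive treatment, by arm, as post-randomisation events. Say that this leaves their clinical management unchanged, and that the office BP at the MD consultation is still taken where possible.

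**Statistical analysis.** State that all randomised patients with a primary outcome are analysed in their allocated group, whether or not one of these events occurred. Keep the complete-case chi-square and add one prespecified sensitivity analysis for missing primary outcomes. Missing = not controlled is one acceptable choice among several.

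**Sample size.** Say what the 10% margin is meant to cover.

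**Cost.** Wording in three sections and one extra analysis. The downside is that outside adjustments become part of the comparison, so the estimate is of offering the APN visit within care as it actually happens. Final BP readings that are never taken cannot be recovered later, so the change belongs before recruitment, or as early in follow-up as possible.
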